#### Assessment of musculoskeletal disturbances

Musculoskeletal symptoms are evaluated by the use of a 50-item self-report questionnaire (see Additional file 1: Appendix C2) [33], which investigates shoulder, arm, elbow, wrist, hand, spine, hip, knee, ankle, and foot problems.

#### Assessment of well-being/depression

Screening for depression is performed by asking participants to fill in the WHO-5 Well-being Index, a five-item questionnaire (see Additional file 1: Appendix C3) [34], which was found to be suitable for use in outpatients with type 1 and T2DM [53].

#### Assessment of health-related QoL

Health-related QoL is evaluated using the Italian version [54] of the SF-36 health survey (ISF-36) (see Additional file 1: Appendix C4) [35], which yields four physical and four mental health component scores and has been previously validated in subjects with T2DM [55, 56]. The physical and mental component summary measures (PCS and MCS, respectively) are normalized to a population mean of 50 and SD of 10.

### Adverse events

Adverse events are reported at intermediate visits and, for INT subjects, also at supervised sessions, by completing a standard form.

### Dissemination policy

Trial results will be communicated to participants via the website of the Metabolic Fitness Association (http://www.metabolicfitness.it/) and by organizing a dedicated event. Results will by also communicated to the scientific via publication and to the public via press release. The final report will follow the main CONSORT 2010 guideline and will be extended as necessary for a non-pharmacological intervention.

After publication of the results, public access to the full protocol, participant-level dataset, and statistical code will be eventually granted upon request.

### Data collection, storage and security

Data collected via web into the IDES_2 database and downloaded from the accelerometers are saved to a password-protected server in the Metabolic Fitness Association. These data are accessed only by members of the research team. Once all data have been uploaded to the server, they will be securely deleted from the recording devices. Patient questionnaire data will be anonymized and stored in locked filing cabinets in the Metabolic Fitness Association.

### Statistical analysis

Sample size calculation is based on preliminary accelerometer data showing that daily PA in sedentary, physically inactive T2DM patients is 24.2 ± 9.4 METs ∙ h^−1^ ∙ wk^−1^. To observe a 15 % increase in daily PA with a statistical power of 90 % (α = 0.05) by unpaired t-test, 142 patients per arm are needed (284 total). A sample size of 300 patients will allow supporting a 5 % dropout rate, as detected in the EXE group from the IDES [14].

The χ^2^ test for categorical variables and the Student’s t test or the corresponding nonparametric Mann–Whitney test for continuous variables will be utilized to compare patients’ characteristics at baseline.

The intent-to-treat analysis for primary and secondary endpoints will be applied to all randomized patients with a baseline and at least one post-baseline value. The efficacy of the intervention, as compared with standard care, on the primary and secondary endpoints will be assessed by a repeated measures analysis of covariance (ANCOVA - using PROC MIXED in SAS software) of change from baseline to the end-of-study. In case of differences between groups in baseline values, we will consider a baseline adjustment to improve power. The differences between end-of-study and baseline QoL scores and summary measures between the two groups will be compared using the Mann–Whitney U-test, while changes in QoL parameters within each group (end-of-study versus baseline) will be tested using the Wilcoxon test.

To account for change in medication throughout the study period, which might affect performance with respect to cardiovascular risk factors, we will perform both multiple regression and sensitivity analyses. In the regression models, the dependent variable will be represented by baseline to end-of-study changes. Treatment at baseline and treatment initiation during the study will be included in the model as dichotomous variables (yes versus no), whereas drug dosage will be not taken into consideration. Sensitivity analysis will be conducted by comparing study arms after exclusion of the patients who modified the treatment.

In order to treat attrition, we will assume that data are missing at random, use adjustment methods for missing data, and conduct a sensitivity analysis to assess the robustness of inferences about treatment effects to various missing-data assumptions [57]. In particular, repeated measures models with an autoregressive correlation type matrix will be applied in order to account for both missingness at random and potential correlation within subjects. These methods are more efficient in that they allow evaluating all subjects, even those with incomplete data [58, 59]. Moreover, to guarantee replicability and avoid outcome selective reporting, a fully specified statistical analysis plan will be written before unmasking.

Statistical analyses will be performed by at the CORE using SAS software release 9.3 (Cary, NC, USA).

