However, it is difficult for people with T2DM to put into action these exercise recommendations for a number of external and internal barriers [21]. Data from trials for T2DM prevention [22, 23] and treatment [24] suggest the need to identify effective strategies to promote an adequate amount of PA in sedentary subjects such as those suffering from metabolic disorders. Unfortunately, available studies have applied PA-targeted behavioral interventions that are either heterogeneous or insufficiently detailed [25]. Moreover, these studies generally involved small samples, and changes in PA were not objectively measured. In the IDES, supervised training, in addition to providing significant health benefits, was successful also in promoting PA outside the supervised sessions, likely by improving patient’s knowledge, confidence, and sureness in his/her ability to perform PA effectively and safely on his/her own.

The IDES_2 is an open-label, parallel RCT aimed at assessing the efficacy of a behavioral intervention strategy derived from the IDES protocol in increasing total daily PA and reducing SED-time in patients with T2DM. This strategy combines the seven-step theoretical exercise counseling [26] provided to all IDES participants [27] with eight bi-weekly sessions, supervised by an exercise specialist in a dedicated gym facility. These sessions, which in the IDES were administered to the intervention group for the entire 12-month study duration [27], serve as a theoretical and practical counseling to promote and maintain a physically active behavior. Intervention is repeated every 12 months for 3 years, and PA is objectively monitored throughout the study by the use of an accelerometer. This intervention strategy is compared with current approach, that is, standard medical care including general physician recommendations on PA.

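### The 5 % dropout allowance is a 12-month figure carried without justification to a 36-month endpoint, and N = 300 leaves almost no slack: about 87 % t-test power if that rate recurred each year

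*Protocol article*

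**What the plan says.** The sample size paragraph (Protocol article, Statistical analysis) starts from preliminary accelerometer data in which "daily PA in sedentary, physically inactive T2DM patients is 24.2 ± 9.4" METs·h⁻¹·wk⁻¹. The target is stated as "To observe a 15 % increase in daily PA", "with a statistical power of 90 % (α = 0.05) by unpaired t-test", which leads to "142 patients per arm are needed (284 total"). The next sentence makes the dropout allowance: 300 patients are said to cover a 5 % "dropout rate, as detected in the EXE group from the IDES".

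On the length of the two trials, the Background says that the supervised sessions "in the IDES were administered to the intervention group for the entire 12-month study duration", so the earlier trial ran for 12 months. Of the present trial it says "Intervention is repeated every 12 months for 3 years". Table 2 places the close-out visit at month 36, and the Statistical analysis section defines the efficacy comparison as change from baseline to end of study.

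The same section plans a repeated-measures ANCOVA in all randomized patients with a baseline and at least one later value. Adjustment for baseline is left as an option to be weighed if the groups turn out to differ at baseline.

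**The concern.** A dropout proportion has meaning only together with the period over which it accrued. Here a proportion observed over 12 months is used as the total loss over 36 months, and the article gives no reason for treating the two as equal. For 5 % to hold over three years, annual loss would have to be 1 − 0.95^(1/3) = 1.7 %, about a third of the rate cited.

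The stated 90 % power depends on this allowance, because the enrolment figure was chosen to cover 5 % and hardly more. The Discussion cites the large sample and long duration together as grounds for robust conclusions, yet the sample size makes no allowance for the duration.

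**Working it through.** **Inputs.** From the Statistical analysis section: mean 24.2, SD 9.4, 15 % increase, α = 0.05, 90 % power, unpaired t-test, N = 300, 5 % dropout. Allocation is 1:1 (Randomization). Sidedness is not stated. A two-sided test reproduces the plan's figure; a one-sided test gives 115 per arm and does not.

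**Step 1: the plan's own figure.** Difference = 0.15 × 24.2 = 3.63. Standardised, 3.63 / 9.4 = 0.386. The noncentral t solution for 90 % power is 141.9, so 142 per arm and 284 in total. Inflation: 284 / 0.95 = 298.9, rounded to 300. Both stated figures reproduce.

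**Step 2: the slack.** 300 × 0.95 = 285 evaluable against 284 needed. The loss at which power equals 90 % is 1 − 141.9 / 150 = 5.4 %.

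**Step 3: other losses.** The documents give no 36-month rate, so I assume a constant annual loss *a*. Then n per arm = 150 × (1 − *a*)³, and power is that of the two-sided t-test with noncentrality 0.386 × √(n/2). At *a* = 5 %: 0.95³ = 0.857; n = 128.6; noncentrality = 0.386 × √64.3 = 3.10. The normal approximation gives Φ(3.10 − 1.96) = 87.2 %, and the exact t-test gives 87.0 %.

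| Assumed annual loss | Loss at month 36 | Evaluable per arm | t-test power |
|---|---|---|---|
| 3 % | 8.7 % | 136.9 | 88.9 % |
| 5 % | 14.3 % | 128.6 | 87.0 % |
| 7 % | 19.6 % | 120.7 | 84.8 % |
| 10 % | 27.1 % | 109.4 | 81.1 % |

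Power stays above 80 % until loss reaches about 29 %. At 5 % per year, keeping 284 evaluable patients would take 284 / 0.857 = 331.2, so 332 randomized.

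**Step 4: what baseline adjustment does.** At 128.6 per arm, the effective SD is 9.4 × √(1 − r²) for a baseline-adjusted analysis and 9.4 × √(2(1 − r)) for an unadjusted change score, where r is the correlation between baseline and month 36. The documents give no r, so both values below are assumptions.

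| r | Baseline-adjusted | Unadjusted change |
|---|---|---|
| 0.3 | 89.9 % | 74.1 % |
| 0.5 | 94.5 % | 87.0 % |

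**The case against.** **Nothing is miscalculated.** This stands. The article says only that 300 can absorb a 5 % loss, which is true. The fault lies in the input chosen, not in the arithmetic.

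**The t-test is not the planned analysis.** The repeated-measures model keeps patients with incomplete follow-up, so less information is lost than completers. This stands in part. I checked a model with baseline means constrained equal, at 5 % loss per year, by normal approximation with assumed correlations. Power at month 36 was about 87 to 89 % for an autoregressive visit-to-visit correlation of 0.5 to 0.8, 93 % at 0.9, and 90.5 % or 95 % for an equal correlation between visits of 0.3 or 0.5. The recovery is therefore small to complete, depending on a correlation the documents do not give. That model also adjusts for baseline, which the article leaves optional. The 90 % itself is stated for a t-test, and the sponsor inflated for dropout on that basis.

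**Retention measures are in place.** The Investigators section describes regular contact, post-trial access to the intervention for both groups, and outcome collection whether or not treatment continues. It also says this strategy was used in the earlier trial, so its effect is already in the 5 %. It does not show that the same total would hold for three times as long.

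**A reader might infer that dropout will be higher here because the 5 % comes from a supervised exercise arm and contact is now much lighter.** The documents do not support this. The Discussion reports that the earlier trial's control group dropped out at a similar rate and for similar reasons. Only the contrast between 12 and 36 months remains.

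**Conclusion.** The 90 % power is not supported on its own stated basis. The dropout allowance is a 12-month figure, the endpoint is at 36 months, no justification links them, and the enrolment figure leaves room for about one patient beyond the requirement. If the cited rate recurred each year, t-test power would be about 87 %, a shortfall of 3 points. The range is about 1 point at 3 % per year to about 9 points at 10 %.

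A reader might go further and conclude that the design fails to deliver 90 % power. That does not follow. The documents give no 36-month dropout rate, constant annual loss is an assumption (losses may be concentrated in the first year), and the planned model uses partial data. Delivered power may lie above or below 90 %. The point is modest in size, but it concerns a headline figure and is cheap to put right.

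**What to change.** Keep N = 300 and make two changes in the Statistical analysis section.

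1. Restate the power with the loss it assumes, for example: *Assuming a loss of 5 % per year (about 14 % at 36 months), about 257 patients are evaluable, giving about 87 % power by two-sided t-test for a 15 % difference; power is 88.9 %, 84.8 % and 81.1 % at annual losses of 3 %, 7 % and 10 %.* If the sponsor has grounds for expecting only 5 % over three years, state them instead.

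2. Replace the optional baseline adjustment with a fixed rule: *All primary analyses will be adjusted for the baseline value of the outcome, whether or not the groups differ at baseline.* At 14 % loss this gives about 90 % power if the baseline-to-month-36 correlation is 0.3 and 94.5 % if it is 0.5. State the correlation as an assumption. Under the planned autoregressive structure it may be low: a visit-to-visit value of 0.8 implies 0.8⁹ = 0.13 over nine visits, and 0.9 implies 0.9⁹ = 0.39.

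The cost is a slightly less favourable stated power. No extra patients, visits or measurements are needed. Restoring 90 % by numbers alone would need about 332 patients at 5 % loss per year; I do not recommend it, because adjustment costs nothing.

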#### Assessment of modifiable cardiovascular risk factors

The following modifiable cardiovascular risk factors are being evaluated at baseline, end-of-study, and every 4 months in-between: HbA_1c;_ fasting plasma glucose (FPG); serum insulin; C-peptide; BMI; waist circumference; body composition; BP; triglycerides; total, LDL and HDL cholesterol; high sensitivity-C-reactive protein (hs-CRP); aspartate aminotransferase (AST); alanine aminotransferase (ALT); γ-glutamyl-transpeptidase (γ-GT); creatine kinase (CK); complete blood count; uric acid; blood urea nitrogen (BUN); serum creatinine; urinalysis; and albumin/creatinine ratio on first-voided urine samples.

Body weight and height are measured using a scale and stadiometer, and BMI is then calculated as weight (kg)/height (m^2^), whereas waist circumference is taken at the umbilicus. Body composition is evaluated by assessing the fat mass and fat-free mass by the use of a body fat monitor (Tanita BF664, Vernon Hills, IL, USA). BP is recorded with a sphygmomanometer after a 5-minute rest while the patient remains seated with the arm at the heart level.

Biochemical tests are centralized at the Laboratory of Clinical Chemistry of Sant’Andrea Hospital, an accredited and ISO9001 certified structure, using standard analytical techniques (Table 6). The Homeostasis Model Assessment-Insulin Resistance (HOMA-IR) index is calculated from the FPG and insulin levels [50]. The glomerular filtration rate (GFR) is estimated from the serum creatinine by the use of the Chronic Kidney Disease Epidemiology Collaboration (CKD-EPI) equation [51]. Global and fatal CHD 10-year risk scores are calculated using the United Kingdom Prospective Diabetes Study (UKPDS) risk engine [52].

**Table 6 Tab6:** Laboratory tests

Analyte	Method	Manufacturer
HbA_1c_	HPLC (Adams TMA1C HA-8160)	Menarini Diagnostics, Florence, Italy
FPG	VITROS 5,1 FS Chemistry System	Ortho Clinical Diagnostics Inc, Raritan, NJ, USA
Insulin	Chemiluminiscent immunometric assays (Immulite 2000 Thes)	Diagnostic Products Corporation, Los Angeles, CA, USA
C-peptide	Chemiluminiscent immunometric assays (Immulite 2000 Thes)	Diagnostic Products Corporation, Los Angeles, CA, USA
Triglycerides	VITROS 5,1 FS Chemistry System	Ortho Clinical Diagnostics Inc, Raritan, NJ, USA
Total cholesterol	VITROS 5,1 FS Chemistry System	Ortho Clinical Diagnostics Inc, Raritan, NJ, USA
LDL cholesterol	VITROS 5,1 FS Chemistry System	Ortho Clinical Diagnostics Inc, Raritan, NJ, USA

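### One ANCOVA of change is named for all endpoints outside QoL, with no provision for laboratory values that are likely to be right-skewed and baseline adjustment only if the groups differ (minor)

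*Protocol article*

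**What the plan says.** The Statistical analysis section of the protocol article gives one efficacy method: the effect of the intervention "on the primary and secondary endpoints will be assessed by a repeated measures analysis of covariance", run in PROC MIXED, "of change from baseline to the end-of-study". No scale is stated and no transformation is mentioned.

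Baseline adjustment is conditional: "In case of differences between groups in baseline values, we will consider a baseline adjustment to improve power".

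Non-normality is recognised in two places. For efficacy, "QoL scores and summary measures between the two groups will be compared using the Mann–Whitney U-test". For the table of baseline characteristics, the t test or the "corresponding nonparametric Mann–Whitney test for continuous variables will be utilized to compare" the groups. Neither provision reaches the efficacy analysis of the laboratory values.

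Modifiable cardiovascular risk factors are a secondary objective (Outcome measures). The section on their assessment lists triglycerides, serum insulin, hs-CRP, AST, ALT, gamma-GT, CK and the "albumin/creatinine ratio on first-voided urine samples", among others. A further regression for these factors also takes the change as dependent variable. It and its sensitivity analysis deal with medication changes, not with skewness.

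The same section promises a fully specified SAP before unmasking. That SAP is not available here.

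**The concern.** The eight analytes are positive quantities that often have a long right tail and tend to change in proportion to their starting value. For such data the arithmetic change has a variance that rises with the level, so patients with very high values dominate both the mean difference and its standard error. A common-variance normal model weights them badly. If baseline is also left out of the model, the regression of change on starting value stays in the residual.

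At stake are efficiency and a stable, interpretable effect estimate for part of the secondary endpoints. There is also a question of timing. The trial is open-label and has many secondary endpoints, so the scale of each should be settled before anyone sees results by arm.

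**Working it through.** **The plan's own figure.** Inputs: mean 24.2, SD 9.4, 15% increase, 90% power, α = 0.05. The difference is 0.15 × 24.2 = 3.63. Then n = 2 × (1.96 + 1.2816)² × 9.4² / 3.63² = 140.9, so 141 per arm. The exact t-test solution is 141.9, so 142. The stated 142 per arm reproduces with a two-sided test. It concerns daily physical activity only, and no power is claimed for any laboratory value.

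**Assumptions for the check.** The article gives no SD or distribution for any analyte. I take a lognormal value at baseline and at one follow-up, log-SD s from 0.5 to 1.3, log-scale correlation ρ of 0.5 or 0.7, a true ratio r = 0.85, and 142 evaluable patients per arm.

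**Formulas.** In units of the baseline mean, let v = exp(s²) − 1 and c = exp(ρs²) − 1. The arithmetic effect is 1 − r = 0.15.

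- Arithmetic change, no covariate: SE² = [(2v − 2c) + ((1 + r²)v − 2rc)] / 142.
- Arithmetic change with baseline: SE² ≈ (1 − k²)(1 + r²)v / 142, with k = c/v.
- Log scale with log baseline: SE = s√(1 − ρ²) × √(2/142); the effect is −ln 0.85 = 0.1625.
- Power ≈ Φ(effect/SE − 1.96).

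**One case by hand: s = 0.5, ρ = 0.5.** v = 0.2840, c = 0.1331, k = 0.469.

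- Change alone: SE = √((0.3018 + 0.2629)/142) = 0.0631; z = 2.38; power 66%.
- Change with baseline: SE = √(0.3817/142) = 0.0518; z = 2.89; power about 82%.
- Log scale: SE = 0.5 × 0.866 × 0.1187 = 0.0514; z = 3.16; power about 88%.

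In this case the scale costs about 6 points and the missing covariate about 16.

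**Simulation.** 4,000 runs per setting; the two ends of each range are ρ = 0.5 and 0.7.

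| log-SD | Change alone | Change with baseline | Log scale with baseline | Lost by scale alone | Lost further without baseline |
|---|---|---|---|---|---|
| 0.5 | 68–86% | 83–93% | 89–96% | 3–6 | 7–15 |
| 0.75 | 30–43% | 43–54% | 57–72% | 14–18 | 11–13 |
| 1.0 | 16–21% | 22–28% | 35–47% | 13–19 | 6–7 |
| 1.3 | 8–11% | 12–13% | 23–31% | 11–18 | 2–4 |

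The last two columns are differences of the rounded figures. Repeat runs move them by a point or two, so about 12 to 20 points is a fair summary of the scale effect at log-SD 0.75 to 1.0.

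**A second set-up.** Here the effect was sized to give 90% power on the log scale. Change with baseline then has 85% power at log-SD 0.5, 73–75% at 0.8 and 63–67% at 1.0. Change alone has 67–73%, 54–58% and 42–45%. The direction is the same, but the number of points lost depends on the assumed effect.

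**Influence.** With ρ = 0.7, the 14 most extreme of 284 patients (5%) hold about 43% of the sum of squares of the arithmetic change at log-SD 0.5, 59% at 0.8 and 69% at 1.0. Under normality they hold about 28%.

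**Type I error.** It stayed at about 4 to 6% for every method.

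**The case against.** The strongest reply is that this is SAP detail. A journal article need not list which analytes are log-transformed, and a full SAP is promised. A mixed-model ANCOVA of log values would still fit the sentence in the article. A reader might infer that the article fixes an analysis of raw change. It does not: it never says raw and excludes no transformation. Arithmetic change is only the plain reading where no scale is named.

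A reader might also infer that real improvements in these risk factors will be missed. The documents do not support that. No distribution is given for any analyte. Table 1 excludes macroalbuminuria, which trims the upper tail of the albumin/creatinine ratio at entry. At log-SD 0.5 the arithmetic analysis with baseline still has 83–93% power in the check.

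The simulated data follow the lognormal, proportional-effect model that favours the log analysis. The 15% reduction is borrowed; the article uses 15% only for physical activity. One follow-up value also simplifies a repeated-measures plan with laboratory values every 4 months. The gap between change alone and the log analysis mixes two causes, and only part of it is due to scale.

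All of this stands and limits the point. What remains is that the article does choose methods by endpoint, allows for non-normality in QoL and in the baseline table but not here, and makes a useful baseline covariate depend on an observed imbalance. That last choice is in the text, not merely left open.

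**Conclusion.** The point holds as a minor one. The only efficacy model named outside QoL makes no provision for laboratory values that are likely to be skewed, and it adjusts for baseline only on condition. If those values are roughly lognormal, the scale alone costs about 3 to 6 points of power at log-SD 0.5 and about 12 to 20 points at 0.75 to 1.0. Leaving out baseline costs a further 6 to 15 points over the same range. These sizes rest on the assumed log-SDs, correlations of 0.5 to 0.7, a 15% reduction and a single follow-up. They are not the power of the planned model.

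The loss is confined to efficiency and to the influence of outliers on some secondary laboratory endpoints. False-positive risk, the two primary outcomes and the sample size are not affected. Endpoints such as HbA1c, BMI, waist and blood pressure are not obviously affected by the scale question.

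**What to change.** Add one sentence to the Statistical analysis section, or to the promised SAP before unmasking:

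> Triglycerides, insulin, hs-CRP, AST, ALT, gamma-GT, CK and the albumin/creatinine ratio are analysed with the same PROC MIXED model on the log scale, always with log baseline as a covariate, and reported as ratios of geometric means with 95% confidence intervals.

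Physical activity, sedentary time, HbA1c, BMI, waist and blood pressure can stay on their original scale. A rank test of the change is a weaker remedy: where the log analysis had 90% power, it had 72–77% at log-SD 0.5 and 64–71% at 1.0.

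The change needs no new data or software, since baseline values are already collected. The small downside is that these effects appear as percentage ratios instead of absolute differences.

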### Randomization

Patients are randomized 1:1 to an intervention (INT) group (*n* = 150), receiving a theoretical and practical exercise counseling on top of standard care, and a control (CON) group (*n* = 150), receiving only standard care including general physician recommendations for daily PA.

Randomization is stratified by center and, within each center, by age and type of diabetes treatment (non-insulin versus insulin therapy), using a permuted-block randomization software that randomly varies the block size. To ensure allocation concealment, randomization is centralized at the Center for Outcomes Research and Clinical Epidemiology (CORE). After randomization, participants, physicians and exercise specialists are unblinded to group assignment, as blinding is not feasible in exercise-intervention studies.

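### Randomization is stratified by center, age and insulin use, but the QoL test is fixed as unstratified and the mixed model does not name the strata

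*Protocol article*

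**What the plan says.** Protocol article, Randomization: "Patients are randomized 1:1 to an intervention (INT) group" and a control group, by permuted blocks of varying size. "Randomization is stratified by center and, within each center, by age and type of diabetes treatment (non-insulin versus insulin therapy"). The article does not give the age categories.

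Protocol article, Statistical analysis: for primary and secondary outcomes alike, efficacy "will be assessed by a repeated measures analysis of covariance (ANCOVA - using PROC MIXED in SAS software) of change from baseline to the end-of-study". The covariates of this model are not listed. The one adjustment mentioned is conditional: "In case of differences between groups in baseline values, we will consider a baseline adjustment to improve power".

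For QoL a different method is fixed: "The differences between end-of-study and baseline QoL scores and summary measures between the two groups will be compared using the Mann–Whitney U-test".

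Baseline treatment does appear as a yes/no variable, but only in the supplementary regressions that deal with medication changes and cardiovascular risk factors. The same section promises a complete statistical analysis plan before unmasking.

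**The concern.** Blocking within strata forces the arms to be nearly balanced on center, age and insulin use. That removes the between-stratum part from the true sampling variance of the treatment difference. An analysis that omits the strata leaves that part in the residual, so the reported standard error is larger than the true one whenever the strata predict the outcome. Intervals are then wider than the design warrants, and the test rejects less often than its nominal level under the null.

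The conditional baseline adjustment does not cover this. It concerns baseline values that turn out to differ between arms, whereas stratified blocking is there to prevent imbalance on these factors. A rule triggered by imbalance would therefore not be expected to bring them in. What is at stake is precision, not bias or a raised false-positive rate.

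**Working it through.** **Inputs from the article (Statistical analysis).** "daily PA in sedentary, physically inactive T2DM patients is 24.2 ± 9.4 METs" (mean 24.2, SD 9.4); a 15% increase, so the difference is 0.15 × 24.2 = 3.63; "with a statistical power of 90 % (α = 0.05) by unpaired t-test, 142 patients per arm are needed (284 total").

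**Reproducing the plan's figure.** The two-sided normal approximation gives 141 per arm and the exact noncentral t gives 142 (power 0.9002). A one-sided test would need 115, so the plan is two-sided. For dropout, 284/0.95 = 298.9, or 299, consistent with "A sample size of 300 patients will allow supporting a 5 % dropout rate". The planning test is an unstratified t-test.

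**Input not in the article.** R², the share of variance in the analyzed outcome explained by the strata. It is varied from 0 to 0.30 as an assumption.

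**Formulas**, with allocation balanced within strata and total SD held at 9.4:
- Unadjusted reported SE = 9.4 × √(2/142) = 1.116; 3.63/1.116 = 3.254.
- True SE = 1.116 × √(1 − R²), so the overstatement factor is 1/√(1 − R²).
- Unadjusted type I error = 2 × [1 − Φ(1.96/√(1 − R²))].
- Unadjusted power = Φ[(3.254 − 1.96)/√(1 − R²)].
- Adjusted power = Φ[3.254/√(1 − R²) − 1.96].

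| Assumed R² | SE factor | Unadjusted type I error | Unadjusted power | Adjusted power | Loss (points) |
|---|---|---|---|---|---|
| 0 | 1.00 | 5.0% | 90.2% | 90.2% | 0 |
| 0.02 | 1.01 | 4.8% | 90.4% | 90.8% | 0.3 |
| 0.05 | 1.03 | 4.4% | 90.8% | 91.6% | 0.8 |
| 0.10 | 1.05 | 3.9% | 91.4% | 92.9% | 1.5 |
| 0.20 | 1.12 | 2.8% | 92.6% | 95.3% | 2.7 |
| 0.30 | 1.20 | 1.9% | 93.9% | 97.3% | 3.4 |

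The loss is taken from unrounded powers. It peaks at about 3.5 points near R² = 0.36.

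**Simulation check.** 4,000 trials per setting; 284 patients; 3 centers × 2 age groups × 2 treatment types; blocks of 4 or 6; normal outcome at one time point. The two age groups, the block sizes and 25% on insulin are assumptions. Monte Carlo error on a 5% rate is √(0.05 × 0.95/4000) = 0.3 points.

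| R² | Type I error: t-test / Mann–Whitney / adjusted | Power: t-test / Mann–Whitney / adjusted |
|---|---|---|
| 0 | 4.7 / 4.7 / 4.7% | 90.0 / 88.4 / 90.0% |
| 0.05 | 4.2 / 4.3 / 4.8% | 89.5 / 87.7 / 90.3% |
| 0.10 | 3.5 / 3.5 / 4.5% | 90.9 / 89.7 / 92.6% |
| 0.20 | 3.1 / 3.3 / 5.1% | 92.3 / 90.5 / 95.1% |
| 0.30 | 2.0 / 1.9 / 4.9% | 93.2 / 91.8 / 97.4% |

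The Mann–Whitney test becomes conservative just as the t-test does, while the linear model with strata as main effects stays near 5%. The van Elteren test itself was not simulated.

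**The case against.** The strongest objection concerns the mixed model. It is called an analysis of covariance, its covariate list is left open, nothing excludes the strata, and a full analysis plan is promised. An article commonly leaves a covariate list to that document. This stands: a reader might infer that the primary analysis ignores the strata, but the text shows only that it does not name them. For QoL the objection fails, because the named test is a two-sample test that takes no strata.

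Second, the effect depends on an unknown R². The analysis is of change from baseline, where stable differences between ages, centers or insulin users partly cancel, and the SD of 9.4 is for activity level rather than change. This also stands. A reader might infer that every interval in the trial is too wide; the article does not establish that for any endpoint.

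Third, no promised property fails. Sample size was planned on an unstratified t-test, and that comparison keeps about 90% power or more across the range. A reader might set adjusted power at R² = 0.20 (95.3%) against the stated 90% and infer a loss of 5 points. That is the wrong comparator: unadjusted power at the same R² is 92.6%, so the loss is 2.7 points.

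What remains is an improvement in efficiency, using data that are already collected.

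**Conclusion.** The point holds as one of precision and pre-specification. The QoL comparison is fixed as unstratified after stratified randomization, and the efficacy model mentions only a conditional baseline adjustment. If the strata explain 5% to 20% of the variance of the analyzed outcome, leaving them out overstates the standard error by about 3% to 12%, lowers the real type I error to about 4.4% to 2.8%, and gives up about 1 to 3 points of power compared with an adjusted analysis. At R² = 0 there is no effect.

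These sizes rest on the assumed R² range and on a single-time-point, normal-outcome approximation to the repeated measures model. The error is in the conservative direction: the trial's validity and its planned 90% power stand.

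**What to change.** In the Statistical analysis section, or in the analysis plan before unmasking, state that the PROC MIXED model always includes center, age group in the categories used for randomization, and diabetes treatment at randomization (insulin versus non-insulin) as main effects, whatever balance is observed. For QoL, replace the unstratified Mann–Whitney test with a van Elteren test on the same strata, or analyze the scores in the same adjusted mixed model.

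The cost is a sentence or two. All three factors are known from randomization. With two age groups (an assumption) they use 2 + 1 + 1 = 4 degrees of freedom out of roughly 280. Some center-by-age-by-treatment cells may be sparse, so the model should carry main effects rather than the full cross.
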